# Baidu Jieduan granules, traditional Chinese medicine, in the treatment of moderate coronavirus disease-2019 (COVID-19): study protocol for an open-label, randomized controlled clinical trial

**DOI:** 10.1186/s13063-021-05418-y

**Published:** 2021-07-22

**Keywords:** COVID-19, Baidu Jieduan granule, Efficacy and safety, Randomized controlled trial

## Abstract

**Background:**

Currently, coronavirus disease-2019 (COVID-19) is continuously and rapidly circulating, resulting in serious and extensive effects on human health. Due to the absence of antiviral medicine for COVID-19 thus far, there is a desperate need to develop effective medicine. Traditional Chinese medicine (TCM) has been widely applied in the treatment of epidemic diseases in China, with the aim of achieving clinical efficacy and decreasing the use of antibiotics and glucocorticoids. The aim of this study was to evaluate the efficacy and safety of Baidu Jieduan granules in treating COVID-19.

**Methods/design:**

This multicentre, open-label, randomized controlled trial will be conducted in 300 patients with COVID-19. The patients will be randomly (1:1) divided into a treatment group and a control group. All patients will receive standard therapy at the same time. Patients in the experimental group will receive Baidu Jieduan granule treatment twice a day for 14 days. The outcomes will be assessed at baseline and at 3, 5, 7 and 14 days after treatment initiation. The primary outcome will be the rate of symptom (fever, fatigue and coughing) recovery. Adverse events (AEs) will be monitored throughout the trial.

**Discussion:**

The study will provide high-quality clinical evidence to support the efficacy and safety of Baidu Jieduan granules in the treatment of moderate COVID-19, and enrich the theory and practice of TCM in treating COVID-19.

**Trial registration:**

Chinese Clinical Trial Registry ChiCTR2000029869. Registered on 15 February 2020

**Supplementary Information:**

The online version contains supplementary material available at 10.1186/s13063-021-05418-y.

## Introduction

An outbreak of coronavirus disease-2019 (COVID-19) in Wuhan city, China, has resulted in a global health emergency, with over 61.8 million confirmed cases, including over 1.4 million deaths as of 29 November 2020 around the world [1]. The number of patients may be underestimated due to asymptomatic individuals or individuals with moderate symptoms [2]. At present, scientists are sure that COVID-19 is caused by a new virus, named “severe acute respiratory syndrome coronavirus 2 (SARS-CoV-2)” [3]. Patients suffer from fever, fatigue and dry cough, with some progressing to breathing difficulties, acute respiratory distress syndrome or sepsis [4]. The disease is diagnosed by clinical characteristics, epidemiological history and laboratory test results according to the “Guidelines for the Diagnosis and Treatment of Novel Coronavirus (COVID-19) Infection by the National Health Commission (Trial Version 7)” [5].

Currently, there are no vaccines or specific antiviral drugs for COVID-19; meticulous supportive therapies are the cornerstone. Traditional Chinese medicine (TCM) has an extensive clinical history in preventing and treating epidemic diseases [6]. From the Ming Dynasty, “Wen Yi Lun”, a famous ancient medical book, mentions that epidemic diseases can be contagious to other people and transmitted through the respiratory tract and digestive tract. Modern medical practitioners have suggested that COVID-19 should be classified as damp-warm pestilence in TCM [7]. Dampness obstructs the Qi mechanism, leading to more dampness and warmth. Furthermore, damp warmth may also injure Yin and Qi and cause pathogenic toxicity and blood stasis. TCM has been widely applied to cure patients with COVID-19 associated with damp-warm syndrome, especially in combination with Western medicine, and can reduce the use of antibiotics and glucocorticoids [8]. Based on the above TCM pathogenesis of COVID-19, our team proposes “San Tong strategies” [9], integrating three kinds of strategies, including relief of the exterior syndrome, diarrhoea and diuresis, and the “truncation and reversion” strategy [9, 10], rationally adopting catharsis of the large intestine to prevent and treat sepsis and prevent and treat the disease in a timely manner. On the foundation of the San Tong strategies, we developed Baidu Jieduan granules, a formula consisting of *Rheum palmatum L.* stem (*Dahuang*), *Sargentodoxa cuneata (Oliv.) Rehd. et Wils.* (*Hongteng*), *Taraxacum mongolicumHand.-Mazz.* (*Pugongying*), *Raw Gypsum* (*Sheng Shigao*), Herba Ephedra (*Mahuang*), *Talcum* (*Huashi*), *Amygdalus Communis Vas* (*Xingren*), *Radix Glycyrrhizae* (*Gancao*), *Verbena officinalis L.* (*Mabiancao*), *Polygonum cuspidatum* (*Huzhang*), *Scutellariae Radix* (*Huangqin*) and *Bombyx batryticatus* (Jiangchan).

Baidu Jieduan granules evolved from the classical TCM prescription Maxing Shigan decoction and our experiential prescription, Jinhong decoction. Our previous studies have demonstrated that Jinhong decoction, composed of *Rheum palmatum L.* stem, *Sargentodoxa cuneata* and *Taraxacum mongolicum*, can inhibit the levels of TNF-α, IL-6, IL-8 and other inflammatory cytokines; protect against excessive inflammatory responses; and maintain an organism’s balance between inflammation and anti-inflammatory responses in infectious diseases [11, 12]. Recent research has shown that Maxing Shigan decoction is regarded as an antipyretic, anti-inflammatory, antiviral, antitussive and antiasthmatic agent and can be used to treat COVID-19 [13]. Therefore, Baidu Jieduan granules should have beneficial and curative effects on COVID-19. However, there is insufficient evidence to show the clinical efficacy of Baidu Jieduan granules. Hence, we aim to conduct a multicentre, randomized trial to evaluate the efficacy and safety of Baidu Jieduan granules in the treatment of COVID-19. Furthermore, this trial can serve as a reference for TCM in the prevention and treatment of COVID-19 worldwide.

## Methods/design

### Study design and settings

The study is designed as a randomized, placebo-controlled, multicentre trial, which will be conducted at four medical centres selected by the expert committee: the Huangshi Hospital of Traditional Chinese Medicine; Tongji Hospital, Tongji Medical College, Huazhong University of Science and Technology; LaoHeKou Traditional Chinese Medicine Hospital; and Leishenshan Hospital of Wuhan. A total of 300 participants fulfilling the eligibility criteria will be randomized into two groups (Baidu Jieduan granule group and control group) at a ratio of 1:1. The study flowchart is illustrated in Fig. 1. The Standard Protocol Items Recommendations for Interventional Trials (SPIRIT) checklist is presented in Additional file 1.

**Fig. 1 Fig1:**
[figure not shown]
The flow chart of the efficacy and safety of Baidu Jieduan granules for moderate COVID-19. COVID-19: coronavirus disease-2019

### Population

Participants with COVID-19 will be recruited from 4 study sites in China. Patients who are eligible according to the inclusion criteria and who provide informed consent will be screened during the clinical trial period. Patients meeting any of the exclusion criteria will be excluded before randomization. Recruitment will last for 5 months, from February 2020 to December 2020.

### Inclusion criteria

Subjects must meet all of the following requirements:
Patients 18–85 years of agePatients with COVID-19 confirmed by SARS-CoV-2 nucleic acid testing of respiratory specimens showing positive resultsPatients providing written informed consent

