### Sample size

A similar clinical trial has been conducted using TCM to decrease the rate of symptoms (fever, fatigue and coughing) in patients with COVID-19 [14]. The rate of recovery of clinical symptoms was 91.2% in patients who received TCM treatment and 61.1% in patients who received conventional treatments. Considering 90% power with a significance level of 10%, as well as a rate of withdrawal and loss to follow-up of 10% [15], we plan to recruit at least 150 participants in each group to achieve sufficient precision in a subsequent full trial.

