### Outcomes and measurements

The primary outcome will be the proportion of negative SARS-CoV-2 nucleic acid results on the 14th day. The secondary outcomes will be the time to symptom recovery, the proportion of cases with reversion on chest CT, the time to negative SARS-CoV-2 nucleic acid results and the proportion of participants regrouped as severe cases. Symptom recovery is defined as the complete disappearance of fever, fatigue and coughing symptoms.

Evaluation of the primary and secondary outcomes will occur at five points (before treatment and the 3rd, 5th, 7th and 14th days of hospitalization).

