### Statistical analysis

We will not conduct subgroup or adjusted analyses of the trial. The independent statistical analysts will be responsible for the data analysis. All patients will be analysed on the basis of intent-to-treat analysis, including all randomized subjects who take Baidu Jieduan granules at least once and have follow-up information recorded. In the case of missing data, multiple imputation will be carried out to generate missing values. A per-protocol analysis, which includes patients who completed the trial without conflict with the major protocol, can be conducted as appropriate. Then, the statistician will submit statistical reports in a timely manner to the study director. The statistical analysis will be performed in a blinded manner using SPSS 20.0 software. Continuous variables characterizing each study group will be expressed as the mean with standard deviation or median with interquartile range. Categorical variables will be reported as frequencies and proportions. Continuous outcomes will be analysed by unpaired Student’s *t*-test or Wilcoxon’s nonparametric statistic, while count data will be compared using a chi-square test or Fisher’s exact test. All statistical tests will be two-sided. *P* < 0.05 will be considered statistically significant. We will not carry out an interim analysis.

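### Neither eligibility nor the Methods' day-14 viral outcome requires a positive test at baseline, so patients already negative before treatment can enter and count as successes in both arms

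*Protocol article*

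**What the plan says.** All references are to the protocol article.

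- **Inclusion criteria.** The list opens with "Subjects must meet all of the following requirements" and has three items: age, consent, and disease "confirmed by SARS-CoV-2 nucleic acid testing of respiratory specimens showing positive". The test carries no date and is not tied to randomisation.
- **Exclusion criteria.** None concerns patients who have already turned negative, or time since diagnosis or onset. Time limits do appear for other items: 6 months for immunosuppressants or transplant, and 30 days for other trials.
- **Outcomes and measurements.** "The primary outcome will be the proportion of negative SARS-CoV-2 nucleic acid results on the 14th day". Time to a negative result is a secondary outcome. Assessments are set at "before treatment and the 3rd, 5th, 7th and 14th days of hospitalization". The pre-treatment result defines neither who may enter nor who is in the denominator.
- **Statistical analysis.** "We will not conduct subgroup or adjusted analyses of the trial".
- **Abstract.** A different primary outcome is named: "The primary outcome will be the rate of symptom (fever, fatigue and coughing) recovery".

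**The concern.** The Methods' primary outcome is a state on day 14, not a change from positive to negative. A patient who is negative on the pre-treatment sample and stays negative is a success whichever arm he or she is in. Such a patient carries no information on whether treatment speeds viral clearance. Each one raises the success proportion in both arms and pulls the two proportions together. In the time-to-negative outcome the same patients have nothing to convert, and would enter with a time of zero or an undefined time.

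Two things are at stake: the size of the estimated effect, which would understate the effect in patients who are still positive, and possibly power. This is separate from any question about severity or symptom criteria, because a symptomatic patient can also be test-negative at baseline.

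**Working it through.** **Does any stated rule close the gap?** Eligibility does not require baseline positivity. The pre-treatment assessment exists but is not used. Subgroup and adjusted analyses are ruled out, so baseline viral status is not handled there. The Patient withdrawal section allows withdrawal on recovery, but that acts after enrolment and is not defined by viral status.

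**The plan's own figure.** The article gives no expected rate for day-14 viral negativity. Its Sample size section rests on another outcome: "The rate of recovery of clinical symptoms was 91.2% in patients who received TCM treatment and 61.1% in patients who received conventional treatments". Those rates with 90% power and a two-sided 10% level give 33 per arm, or 37 after 10% loss (33/0.9 = 36.7), not 150. That mismatch is a separate matter. Only the planned 150 per arm and the 10% loss are used below.

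**Inputs**
- Evaluable per arm: 150 × 0.90 = 135 (Sample size).
- Two-sided 5% level (Statistical analysis).
- f, the share already negative at baseline: not given; 0 to 30% assumed, with 50% as an extreme.
- Rates among patients positive at baseline: not given. Three scenarios are used: 61.1% v 91.2% (borrowed from symptom recovery), and 60% v 78% and 61.1% v 76.1% (both assumed).
- Patients negative at baseline are assumed to stay negative to day 14, with the same f expected in both arms through randomisation.

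**Dilution.** Observed rate in an arm = f + (1-f)p. The difference is [f + (1-f)pT] - [f + (1-f)pC] = (1-f)(pT - pC).

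**Power.** Φ{(d - 1.96·SE0)/SE1}, where SE0 uses the pooled rate and SE1 the separate rates.

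Worked case, 60% v 78%, f = 20%:
- Control: 0.20 + 0.80 × 0.60 = 0.680. Treated: 0.20 + 0.80 × 0.78 = 0.824. Difference d = 0.144.
- Pooled rate 0.752; SE0 = √(0.752 × 0.248 × 2/135) = 0.0526.
- SE1 = √[(0.680 × 0.320 + 0.824 × 0.176)/135] = 0.0518.
- (0.144 - 1.96 × 0.0526)/0.0518 ≈ 0.79, so power is about 79%.

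**Results, all randomised, 135 per arm**

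| True rates | f | Observed rates | Difference (points) | Power |
|---|---|---|---|---|
| 61.1 v 91.2% | 0 | 61.1 v 91.2% | 30.1 | >99% |
| | 20% | 68.9 v 93.0% | 24.1 | >99% |
| | 30% | 72.8 v 93.8% | 21.1 | >99% |
| | 50% | 80.6 v 95.6% | 15.1 | 97% |
| 60 v 78% | 0 | 60.0 v 78.0% | 18.0 | 89.6% |
| | 20% | 68.0 v 82.4% | 14.4 | 78.5% |
| | 30% | 72.0 v 84.6% | 12.6 | 71.2% |
| 61.1 v 76.1% | 0 | 61.1 v 76.1% | 15.0 | 76% |
| | 20% | 68.9 v 80.9% | 12.0 | 62% |
| | 30% | 72.8 v 83.3% | 10.5 | 55% |

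**Baseline-positive patients only, 60% v 78%.** The difference returns to 18 points. With 135 × 0.8 = 108 per arm, power is 82.1%; with 135 × 0.7 = 94.5 per arm, it is 76.7%. The gain over all randomised is about 3.5 points at f=20% and 5.5 points at f=30%.

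**The case against.** **Silence is not permission.** A reader might infer that the trial accepts a positive test of any date. The article does not say that. It is silent, and current infection at screening is a natural reading. The full protocol (version 1.0 under Trial status) and the assessment schedule in Fig. 2 are not shown and may fix the timing. Counting visits in days of hospitalisation also suggests newly admitted patients. This stands as a limit on how many such patients there would be. It does not dispose of the point, because the stated outcome counts a state rather than a conversion, and the stated analysis makes no use of the baseline result.

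**Power may hardly suffer.** A reader might infer that the trial is underpowered for this reason. The documents do not support that. At the only rates in the article, power stays at or above 97% even with half the patients already negative. Those rates are for symptom recovery, so they neither establish nor rule out a loss for viral negativity.

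**No false-positive risk.** A reader might also infer that the comparison is biased in favour of the granules. It is not. Randomisation balances baseline status in expectation and the test of no effect remains valid. The harm is dilution towards no difference.

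**Which outcome is primary?** The Abstract names symptom recovery and the sample size is built on it. If that is what is intended, this point moves to the viral secondary outcomes. That stands.

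**Conclusion.** The point holds as a modest but worthwhile improvement to the outcome definition and analysis set. As written, patients already negative before treatment can be randomised and counted as successes in both arms, and the risk difference is then multiplied by (1-f), for example by 0.8 at f=20%. That factor is exact if such patients stay negative to day 14; some turning positive again would alter it slightly.

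The power consequence cannot be settled from the article. At f=20% it ranges from negligible to a loss of about 11 to 14 points across the three scenarios, and both f and the two smaller effects are assumptions. The certain part is qualitative: the estimated effect is diluted whenever f is above zero and treatment works, and time to negative includes patients with nothing to convert.

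**What to change.** Define the Methods' primary outcome as conversion from positive to negative by day 14. Analyse it, and time to negative, in randomised patients whose pre-treatment sample was positive, and report all randomised patients as a sensitivity analysis. State that this sample is taken before randomisation, so that the subset rests on a pre-randomisation value and the randomised comparison is preserved. Word it as the main analysis set, so that it does not clash with the statement that no subgroup analyses will be done.

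Alternatively, where the result is available in time, require that sample to be positive for entry. The Trial status section says recruitment has begun, so an entry rule would reach only later patients. The analysis-set definition can cover everyone with a suitable sample if it is fixed before outcome data are examined by arm.

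Cost: a sentence or two and no additional scheduled test. The analysis-set route gives a somewhat smaller denominator. It recovers only part of the lost power (about 3.5 to 5.5 points in the 60% v 78% illustration) but restores the undiluted effect estimate. The entry rule excludes some screened patients but, if 135 evaluable per arm are still reached, keeps the full power. If symptom recovery is confirmed as the primary outcome, apply the same definition to the viral secondary outcomes.

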### Exclusion criteria

The exclusion criteria are as follows:
Pregnancy and lactationSevere primary diseases influencing survival, including malignant tumours, haemorrhagic disease and HIVSevere liver and kidney dysfunctionImmunosuppressant therapy or an organ transplant within the previous 6 monthsParticipation in another clinical trial in the last 30 daysAllergy to one or more components in the herbal TCM prescription

### Patient withdrawal

Enrolment without meeting the inclusion criterionUnsuitability for the trial due to deterioration or recovery of the patient’s conditionPoor patient complianceVoluntary withdrawal

Upon patient withdrawal from the trial, all collected data up to the time of withdrawal will remain in the database. Safety-related information may be obtained until the 14th day after withdrawal if possible.

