### Quality control

All investigators of the trial will be trained strictly and comprehensively by the State Food and Drug Administration, following Good Clinical Practice (GCP), to thoroughly comprehend the procedure of the trial and improve compliance. All qualified researchers will collect data and complete the CRF in an accurate and complete manner. After discharge, the subjects will be followed up by phone. Regular monitoring and inspections will be conducted by the CRO once a month to confirm the reliability of the related research data and the trial process. The CRO will check details on informed consent, the inclusion and exclusion criteria, the original data, the management of AEs, the process of storage and distribution of the research drugs and the CRF.

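### Withdrawal for deterioration or recovery ends planned efficacy collection before day 14, so the primary outcome may be missing for reasons tied to the outcome itself

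*Protocol article*

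**What the plan says.** The Patient withdrawal section gives four grounds for leaving the trial: enrolment that turns out not to meet the inclusion criteria, unsuitability "for the trial due to deterioration or recovery of the patient" (the sentence continues with the patient's condition), poor compliance, and the patient's own choice. On data, it says that "all collected data up to the time of withdrawal will remain in the database". For the time after withdrawal it adds only this: "Safety-related information may be obtained until the 14th day after withdrawal if possible". It makes no provision for efficacy data after withdrawal.

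Outcomes and measurements states: "The primary outcome will be the proportion of negative SARS-CoV-2 nucleic acid results on the 14th day". The secondary outcomes there include times to symptom recovery and to a negative test, and "the proportion of participants regrouped as severe cases". Assessments are at baseline and days 3, 5, 7 and 14. The Abstract names a different primary outcome: "The primary outcome will be the rate of symptom (fever, fatigue and coughing) recovery".

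Under Statistical analysis, where data are missing, "multiple imputation will be carried out to generate missing values". Under the second Quality control heading, "After discharge, the subjects will be followed up by phone". Randomization and blinding states that the trial is open-label. The Sample size section allows 10% for withdrawal and loss.

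**The concern.** Recovery and deterioration are what this trial sets out to measure. Symptom recovery is the Abstract's primary outcome, becoming a severe case is a secondary outcome, and both are plausibly related to the day-14 test. The same two events are also grounds for leaving the trial, after which no efficacy measurement is planned. A patient withdrawn on, say, day 8 was last assessed on day 7 and has no planned day-14 test. A patient withdrawn as worsening might never be recorded as regrouped to severe.

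The gaps are to be filled by multiple imputation, which in its standard form assumes that missingness is explained by the observed data in the model. If the model leaves out why a patient left and what the last test showed, values for the withdrawn are borrowed from patients whose course was different. Staff who know the allocation judge unsuitability, so the balance of reasons may differ between arms. The comparison could then be shifted in either direction. A day-14 test that was never taken cannot be recovered at the analysis stage.

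**Working it through.** **Inputs from the protocol article.** 150 per arm and a 10% allowance for withdrawal and loss (Sample size); two-sided 5% test (Statistical analysis). Expected evaluable patients: 150 × 0.90 = 135 per arm. The stated inputs for 150 (91.2% versus 61.1%, 90% power, 10% significance) give only 33 per arm, or 37 after 10% loss. That is a separate matter, and 150 is used here simply as the planned size.

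**Assumptions, not in the documents.** The true day-14 negative rate p is the same in both arms. A share r leaves as recovered, and all of these are truly negative. A share d leaves for deterioration, and all of these are truly not negative. Imputation draws only on completers of the same arm. The documents give no split of withdrawals by reason.

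**Formula.** Estimated rate = (p − r)/(1 − r − d).

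**Worst case: one arm loses only deteriorating patients, the other only recovered patients, p = 0.80.**
- 5%: 0.80/0.95 = 84.2%; (0.80 − 0.05)/0.95 = 78.9%; gap 0.05/0.95 = 5.3 points.
- 10%: 0.80/0.90 = 88.9%; (0.80 − 0.10)/0.90 = 77.8%; gap 0.10/0.90 = 11.1 points.
- Of the 5.3 points, deterioration contributes 84.2 − 80.0 = 4.2 and recovery 80.0 − 78.9 = 1.1. The split depends on p; the total does not.

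**Yardstick.** 95% half-width for the difference: 1.96 × √(2 × 0.8 × 0.2/135) = 0.095, or 9.5 points.

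**False-positive rate with no true effect** (normal approximation, 135 per arm, p from 0.60 to 0.80):
- 10% lost in opposite directions: about 47% to 70%.
- 5% recovered plus 5% deteriorated in one arm, 10% recovered in the other: gap (p − 0.05)/0.90 − (p − 0.10)/0.90 = 0.05/0.90 = 5.6 points; about 15% to 21%.
- Same mix in both arms: gap 0, rate 5%.

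**Balanced reasons.** With p = 0.70, a 5%/5% mix gives (0.70 − 0.05)/0.90 = 72.2% in each arm, and 10% recoveries give (0.70 − 0.10)/0.90 = 66.7%. Each arm's rate is distorted, but the difference is not. If a true difference exists, the same mix in both arms multiplies it by 1/0.90 = 1.11.

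**A real effect can shrink.** Take the Sample size rates, which are for symptom recovery and serve here only as an example. If the granule arm loses 10% as recovered and the control arm 10% as deteriorated: (0.912 − 0.10)/0.90 − 0.611/0.90 = 90.2% − 67.9% = 22.3 points, against a true 30.1.

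**The case against.** The strongest reply is that missing at random allows missingness to depend on observed data. Recovery or worsening is seen before the patient leaves, and outcomes are assessed on days 3, 5 and 7. A model using the last test and the withdrawal reason could remove much of the bias. The imputation model commonly belongs in an analysis plan, which is not shown. This stands. A reader might infer that imputation is bound to fail; the documents do not support that, and the missing model is not the finding.

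Other stronger readings also go too far:
- A reader might infer that everyone who recovers or worsens is withdrawn. The ground is a judgement of unsuitability, and how often it would be used is unknown.
- A reader might infer that poor compliance can arise only in the granule arm. The text does not limit it so, and Interventions bars other traditional Chinese medicine in both arms.
- A reader might infer that withdrawn patients drop out of the analysis. Their earlier data are kept and missing values are to be imputed.
- A reader might infer that phone follow-up rules out a day-14 test. The text does not make the phone the only contact, and a call could record a test done elsewhere. A call cannot itself supply one, however, and none is arranged.

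The primary outcome also matters. If the Abstract's symptom recovery is primary, a patient who left as recovered has been seen to recover, and symptoms can be asked by phone, so the concern is weaker. It has full force under the outcome in Outcomes and measurements.

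The illustration is an extreme. It needs opposite reasons by arm and an imputation that ignores earlier data, and the 5.3 points lie inside the half-width. None of this supplies the missing day-14 results.

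**Conclusion.** The concern holds as a fault in the withdrawal and data-collection rule, set against a primary outcome measured on day 14. Followed as written, the plan can leave gaps in the primary outcome that are related to the outcome, and no analysis can replace the uncollected tests. Bias in the comparison is possible rather than certain, and its direction is not fixed.

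The 5.3 and 11.1 points bound a worst case under the assumptions listed; they are not an expected bias. The larger figure exceeds the half-width of 9.5 points and needs the entire planned 10% loss to be outcome-driven. With balanced reasons the false gap largely cancels. The point should be treated as one that must be fixed, because the loss of information is irreversible and the remedy is small. Confidence is moderate, since the frequency of such withdrawals, their split by arm and the imputation model are all unknown.

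**What to change.** Leave the clinical stopping rules unchanged and reconcile Patient withdrawal with Outcomes and measurements:

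1. State that deterioration, recovery, non-compliance and late-found ineligibility end neither outcome follow-up nor inclusion in the intention-to-treat analysis.
2. Collect day-14 nucleic acid result, symptom status and severity status for all randomised patients unless consent is withdrawn, including those discharged.
3. Where the day-14 result is still missing, include withdrawal reason and last nucleic acid result in the imputation model.
4. Add a sensitivity analysis by withdrawal reason. For example, count patients who left as recovered with a documented negative test as negative, and those who left for deterioration or died as not negative. This assignment belongs in a sensitivity analysis, not the main one, because nothing in the documents equates clinical worsening with a positive test.

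The cost is a short amendment and case report form instruction, some effort to obtain tests after discharge, and one extra analysis. The day-14 assessment is already scheduled, and contact for up to 14 days after withdrawal is already foreseen for safety. Trial status expected enrolment to end by 30 December 2020 and the article appeared in July 2021. If data collection has finished, only items 3 and 4 and the analysis-set statement in item 1 can be applied, and the number and reasons of withdrawals should be reported by arm.
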